#### Fiscal mapping process tool

The research team created an initial prototype of the fiscal mapping process (version 1.0) for pilot-testing. The prototype format is an Excel workbook, and it is structured to clearly indicate what information should be entered to complete each step, but also flexible enough to accommodate agencies’ varied strategic planning goals and capture important contextual factors in each step. After specifying the focus of a given fiscal map (EBT, sites, etc.), the user completes the five fiscal mapping process steps: (1) resources needed, (2) funding objectives, (3) financing strategies, (4) fiscal map of EBT, and (5) monitoring plan (see Table 1). A resource tab accompanies each step with other materials useful for completing the step. For example, Step 1 resources include information about EBT time and cost models that help identify resource needs [103] and Step 3 resources summarize the aforementioned compilation of 23 financing strategies for behavioral health [69]. Each resource tab also includes a completed example of the associated step with a hypothetical service agency.

#### Initial training

We will provide a 3-h virtual training to the representatives from each pilot-testing service agency via Microsoft Teams. The agenda includes (a) introductions and project overview (30 min); (b) step-by-step instructions for using the fiscal mapping process, including ample hands-on discussion about completing the tool’s steps for the service agency (2 h); and (c) plans for coaching calls and data collection activities (30 min); regular breaks are included. We will promote engagement in the training through a practical, applied focus that allows agency representatives to leave training with an in-progress fiscal map and concrete next steps for using the tool. We will video-record each training session and give the service agency representatives access to the recording if desired. Two coaches (the principal investigator and project manager) will lead trainings for 5 agencies each; the other coach will attend to provide technical support and record detailed field notes. Both coaches have training in mental health service delivery (clinical psychologist and social worker, respectively) and EBT implementation.

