Ultimately, 12 agencies submitted applications to join the project, of which ten 10 were selected to pilot-test the fiscal mapping process. Four of the participating agencies chose to focus on PCIT for the fiscal mapping the pilot test and the other six to focus on TF-CBT. The two agencies that applied but were not selected both had difficulty identifying service agency and/or funding agency representatives with the capacity to participate in the project (i.e., nominees from the application did not follow through with enrollment).

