#### Monthly coaching

To facilitate the use of the fiscal mapping process, each coach will provide monthly coaching sessions for 1 year with the service agencies for which they led training. Coaching sessions will be brief (~ 15 min per month) and focus on answering the service agency representatives’ practical questions about applying the fiscal mapping process. Prior to each coaching call, the coach will send a structured email inquiry asking representatives to specify (a) which fiscal mapping process steps they have worked on; (b) key areas they wish to prioritize for coaching, such as working toward completion of certain steps or deciding how to share conclusions with stakeholders; and (c) any desired modifications to the session format, like extending the session length or inviting stakeholders to join. The coach will also be available for as-needed consultation outside of the scheduled coaching calls; thus, rather than limiting coaching to 15 min, the use of this brief model provides a sustainable way to maintain monthly coach-agency contact for the duration of pilot-testing. Coaches will record field notes about the frequency, length, modality, and content of each coaching contact in a detailed logbook.

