#### Focus groups

About 3 months after each survey, we will conduct a virtual focus group with each service agency. A given focus group will include one service agency’s representatives; the funding agency representative(s) nominated by the service agency; and an intermediary with expertise in the EBT of focus for pilot-testing (ideally, but not necessarily, the intermediary who nominated the agency). During the focus group, participants will discuss the service agency’s experience with pilot-testing the fiscal mapping process and how using the tool has impacted EBT sustainment capacities (from the Public Health Sustainability Framework [29]; especially financial stability and strategic planning) and outcomes. The groups will also discuss key characteristics of the EBT, agency, and funding context that influence the fiscal mapping process. The coach who does not conduct the agency’s coaching sessions will lead their focus group (to avoid demand effects). Focus groups will be supported by a research assistant who will take detailed notes, and will be audio-recorded for later analysis.

Each focus group is expected to take approximately 1 h, and participants will receive a $50 electronic gift card as compensation. Afterwards, participants will complete a brief web-based survey rating (a) the agency’s capacity for sustaining the chosen EBT using the Program Sustainability Assessment Tool, a measure of Public Health Sustainability Framework domains [56]; (b) extent of EBT sustainment using the three-item Provider REport of Sustainment Scale [106]; and for service agency representatives only (c) intentions to sustain the EBT over the next year. The focus group audio-recordings will be transcribed, with any identifying information removed, and destroyed once the analysis is complete.

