#### Aim 2: evaluation

Our evaluation will primarily rely on the comparative case study approach [92, 93], synthesizing all available quantitative and qualitative data for in-depth insights into each case (i.e., youth mental health service agency that pilot-tested the fiscal mapping process). This approach involves creating descriptive summaries of the role of the fiscal mapping process in EBT sustainment capacities and outcomes at each agency, clearly identifying the contributions of different qualitative and quantitative measures to the conclusions drawn. We will then compare and contrast the ten pilot-testing agencies based on the key characteristics in the sampling plan. At various points in the analysis, a given pair of agencies may be grouped together or contrasted, depending on the characteristic being considered. We will also consider differences in perspective among the three stakeholder participant groups (service agency, funding agency, intermediary). Statistical power is limited, but we will examine if quantitative data follow expected contrasts and patterns over time, such as more effective use of fiscal mapping at agencies with higher and/or increasing strategic planning capacities. We will heavily leverage qualitative data to ensure accurate interpretation and maximize depth of understanding.

To complement our comparative case studies, we will analyze the participatory modeling exercise results to create an overarching conceptual model of the fiscal mapping process that can guide future evaluation. Following the webinar, the project team will review the exercise results and create a system dynamics diagram [94] representing the conceptual model that the participants generated. The system dynamics diagram will specify actors, activities, outcomes, and contextual factors for each step of the fiscal mapping process, providing a visual representation of the complex interactions and feedback loops involved in EBT financing decisions. For specified outcomes of each step, we will also note key indicators for evaluating success. Finally, we will use the conceptual model to expand the Public Health Sustainability Framework [29]—which describes key capacity domains but is silent on how to evaluate their impact—so that the framework can guide prospective evaluations of the fiscal mapping process and other approaches targeting EBT sustainment.

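### Two fixed coach/focus-group-leader pairings are not among the stated cross-agency contrasts, so a difference between pairings could be misattributed to EBT, agency or funding context (minor)

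*Protocol article*

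**What the plan says.** Under Initial training, the protocol article states that "Two coaches (the principal investigator and project manager) will lead trainings for 5 agencies each", and that "the other coach will attend to provide technical support and record detailed field notes". The coaches' backgrounds differ: "Both coaches have training in mental health service delivery (clinical psychologist and social worker, respectively) and EBT implementation". Under Monthly coaching, "each coach will provide monthly coaching sessions for 1 year with the service agencies for which they led training". Session length can be extended and consultation is available on request; "Coaches will record field notes about the frequency, length, modality, and content of each coaching contact in a detailed logbook". Under Focus groups, "The coach who does not conduct the agency’s coaching sessions will lead their focus group (to avoid demand effects".

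On the agencies, the section on service agencies (cases) reports that "Four of the participating agencies chose to focus on PCIT", with the other six on TF-CBT. It lists the features used for sampling: EBT, agency and funding-context characteristics. Under Aim 2: evaluation, "We will then compare and contrast the ten pilot-testing agencies based on the key characteristics in the sampling plan". That section adds contrasts by stakeholder group and by strategic planning capacity over time. None of these contrasts names the coach or the focus-group leader. How agencies were assigned to coaches is not stated.

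**The concern.** The comparative case study is the main method of Aim 2, and its product is an explanation of why the process worked differently at different agencies. Each agency's experience is shaped by the person who trains and coaches it. The account of that experience is then drawn out in a focus group led by the other coach. The two people differ in role and professional background, and the amount of coaching can vary. If agencies under one pairing do better, or describe their experience differently, and those agencies also share an EBT, an agency type or a funding setting, the planned contrasts would offer only the second explanation. With ten cases, one operator pattern could create or hide such a contrast. The article says promising results may lead to a large randomized trial, so a misattributed context effect could carry forward into its design.

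**Working it through.** The plan gives no power, effect size or test for this comparison, so there is no stated figure to reproduce. The counts agree: 4 PCIT + 6 TF-CBT = 10 agencies = 5 + 5 by coach.

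**Step 1: what can be separated.** Let c be the effect on an agency's findings of having the principal investigator rather than the project manager as coach. Let l be the corresponding effect of having the principal investigator rather than the project manager as focus-group leader. Only two combinations occur:

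| Pairing | Coach | Focus-group leader | Agencies |
|---|---|---|---|
| A | principal investigator | project manager | 5 |
| B | project manager | principal investigator | 5 |

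The difference between pairings is D = c − l. The data contain D only; c and l cannot be recovered separately. The swap does not cause this: had each coach led the focus groups of their own agencies, the difference would be c + l, equally inseparable.

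**Step 2: how much of D enters an EBT contrast.** Suppose pairing A has a PCIT agencies and b = 5 − a TF-CBT agencies, and that D is additive. The raw PCIT minus TF-CBT difference is then

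true EBT difference + D × (a/4 − b/6).

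| PCIT split | a, b in the pairing with more PCIT (or equal) | a/4 − b/6 | Leakage (absolute) |
|---|---|---|---|
| 2/2 | 2, 3 | 0.50 − 0.50 = 0 | 0 |
| 3/1 | 3, 2 | 0.75 − 0.33 = 0.42 | 0.42D |
| 4/0 | 4, 1 | 1.00 − 0.17 = 0.83 | 0.83D |

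An exactly balanced split is possible. Complete confounding of pairing with EBT is not, because 4/6 and 5/5 cannot coincide.

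**Step 3: how likely each split is, under an assumption.** The article does not give the assignment method. If agencies had been assigned at random without regard to EBT, there would be C(10,5) = 252 equally likely splits:

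- 2/2: C(4,2) × C(6,3) = 6 × 20 = 120, or 47.6%
- 3/1 either way: 2 × C(4,3) × C(6,2) = 2 × 4 × 15 = 120, or 47.6%
- 4/0 either way: 2 × C(4,4) × C(6,1) = 2 × 1 × 6 = 12, or 4.8%

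The mean absolute leakage would be (120 × 0 + 120 × 0.417 + 12 × 0.833)/252 = 0.24D. These probabilities illustrate the range; they do not describe what happened in this study.

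**Step 4: what a within-coach check offers.** If D is additive, a PCIT versus TF-CBT comparison among agencies of the same coach is free of it. The comparisons available are 2 v 3 and 2 v 3 under a 2/2 split, and 3 v 2 and 1 v 4 under a 3/1 split. Under a 4/0 split there is 4 v 1 for one coach and none for the other.

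**The case against.** A reader might infer that agencies were not balanced by EBT across coaches, and that coach differences would therefore be read as EBT differences. The documents support neither step. The assignment is not described; 2 PCIT and 3 TF-CBT agencies per coach fits the text fully, and a condensed article may leave that detail to the full protocol. The 52% chance of an uneven split (47.6% + 4.8%, rounded) holds only if assignment ignored EBT, and most of it is the milder 3/1 split.

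Nor is the analysis confined to sampling-plan characteristics. It draws on every data source for each case, groups agencies flexibly, and adds stakeholder and capacity contrasts. The coaching log is one of its sources, so coaching intensity is already part of the case evidence.

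There are also safeguards. Both coaches attend every training, and the trainings are video-recorded. A structured email precedes each coaching call. Focus groups follow a semi-structured protocol, with a research assistant taking notes and an audio recording. The sustainment scales are completed by participants in a web survey, so the leader's probing does not score them directly. The swap is itself a deliberate control against demand effects.

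All of this stands, and it moves the claim from would to could. It does not remove the gap. These measures lessen operator influence or record it, but none of the stated contrasts looks for a difference between pairings. The swap protects against agencies pleasing their own coach, which is a different problem.

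**Conclusion.** The point holds in limited form. The article fixes two coach/leader pairings of five agencies each, their component effects cannot be separated, and the pairing is not a stated contrast. A difference D between pairings could therefore be misattributed. In a raw PCIT versus TF-CBT comparison the distortion is between 0 and 0.83D, assuming D is additive. Where this study lies in that range depends on the actual assignment, which the article does not give, and neither does it give the size of D. The same reasoning applies to agency and funding features, but the counts needed to put a figure on those are not given.

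Severity is minor. The evaluation is descriptive, its authors acknowledge limited power and describe most results as preliminary, and no formal test or estimate is invalidated. The missing assignment method is not counted as an error.

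**What to change.** In Aim 2: evaluation:

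1. Name coach/focus-group leader, as one paired characteristic, among the case characteristics used in the cross-agency comparison.
2. Show a table of coach by EBT, and of coach by the key agency features.
3. Before attributing a contrast to EBT, agency or funding context, check whether it also appears among the agencies of each coach, and set it beside the contact frequency and length already in the coaching log.
4. Where the check cannot be made, report the contrast as inseparable from coach.

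Reassigning agencies is probably no longer possible: according to Project timeline, initial training was already under way when the protocol was completed. The cost is one table and one more grouping, with no new data or participants. The downside is that, with five agencies per coach, the within-coach comparisons are very small, some cells may be empty, and some contrasts will have to be left unattributed.

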#### Monthly coaching

To facilitate the use of the fiscal mapping process, each coach will provide monthly coaching sessions for 1 year with the service agencies for which they led training. Coaching sessions will be brief (~ 15 min per month) and focus on answering the service agency representatives’ practical questions about applying the fiscal mapping process. Prior to each coaching call, the coach will send a structured email inquiry asking representatives to specify (a) which fiscal mapping process steps they have worked on; (b) key areas they wish to prioritize for coaching, such as working toward completion of certain steps or deciding how to share conclusions with stakeholders; and (c) any desired modifications to the session format, like extending the session length or inviting stakeholders to join. The coach will also be available for as-needed consultation outside of the scheduled coaching calls; thus, rather than limiting coaching to 15 min, the use of this brief model provides a sustainable way to maintain monthly coach-agency contact for the duration of pilot-testing. Coaches will record field notes about the frequency, length, modality, and content of each coaching contact in a detailed logbook.

#### Plans to address adaptation and fidelity

Throughout the pilot-testing year, we will incorporate feedback from the 48 stakeholder participants into refinements of the fiscal mapping process. If there are major changes to the tool (Version 2.0, 3.0, etc.), then we will re-distribute it to participating agencies and provide additional guidance or training as needed. Thus, we will initially prioritize the adaptability of the fiscal mapping process while we incorporate stakeholder perspectives into the tool. Over time, we will develop a fidelity checklist of core fiscal mapping process steps that can be used by coaches as well as guide fidelity assessments for subsequent evaluations of the strategy.

### Data collection activities and measures

We will collect a mix of quantitative and qualitative data from the expert stakeholder participants for all project aims (see Fig. 1). Data will be collected using secure web-based programs: SelectSurvey for surveys and Microsoft Teams or Zoom.gov video-conference for the focus groups, webinar, and training/coaching activities. We will not collect personally identifiable information; participants will assign each participant a unique, anonymous identification number to identify their data. Table 2 provides a summary of each data collection activity, including the timeframe, measures used, participants involved, compensation amount, and relevant aims.

**Table 2 Tab2:** Data collection activities for developing and evaluating the fiscal mapping process

Activity	Measures	Participants	Time	Compensation	Relevant aims^a^
Web survey #1 (months 1–3)			20–30 min	$30	
	Delphi Round 1	All, separately			Aim 1a
	Feedback on compilation of financing strategies^b^	All, separately			Aims 1b, 2a
	ICS, AFSS	Service agency reps			Aims 1b, 2a
Web survey #2 (months 6–9)		All, separately	20–30 min	$30	
	Delphi Round 2				Aim 1a
	Ratings of characteristics of financing strategies from compilation^b^				Aims 1b, 2a
Focus groups (months 4–5, months 10–11)			60 min	$50 per group	Aim 2a
	Semi-structured protocol	All three types together			
	PSAT, PRESS	All, separately			
	Intentions to sustain	Service agency reps			
	Documents for review	Service agency reps			
Webinar			Up to 120 min	$100	Aim 2b
	Delphi Round 3 (live voting)	All project participants			
	Participatory modeling exercise	together			
Field notes (training notes, coaching log, etc.)		Service agency reps	As relevant	n/a	Aims 1b, 2a

*Note*. ^a^See Fig. 1 for details of the project aims and how they relate to each other. ^b^Refers to the previously published compilation [69] incorporated into the fiscal mapping process. *AFSS* Agency Financial Status Scales [104], *ICS* Implementation Climate Scale [105], *PSAT* Program Sustainability Assessment Tool [56], *PRESS* Provider REport of Sustainment Scale [106]

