**Fig. 1 Fig1:**
[figure not shown]
Overview of the research design for developing and evaluating the fiscal mapping process

Aim 1 is to develop the fiscal mapping process by adapting the intervention mapping process [74] and incorporating our compilation of financing strategies [69]. We will use a modified Delphi technique [91] to obtain formative stakeholder feedback. Delphi is a structured approach to group decision-making, and previous research has established its use for developing consensus about implementation strategies [66]. Sub-aims are to (1a) achieve consensus among our participants—through two web-based survey rounds followed by a round of live, virtual voting—on the key steps of the fiscal mapping process, while (1b) incorporating additional information into the financing strategy compilation to more fully inform strategy selection.

Aim 2 is to evaluate the preliminary impact of the fiscal mapping process. Our 2-year timeline is too short to observe sustainment trajectories, so we will instead focus on short-term factors related to EBT sustainment. Specifically, we will (2a) examine EBT sustainment capacities (e.g., for strategic planning) [29, 56] and outcomes (e.g., intentions to sustain) at the ten pilot-testing service agencies using a comparative case study approach [92, 93]. Each agency that pilot-tests the fiscal mapping process will be considered a case, and we will draw on multiple data sources (i.e., surveys, focus groups, document review, field notes) to compare and contrast experiences across agencies. Following pilot-testing, participants will contribute to a conceptual model of fiscal mapping’s process and outcomes through a participatory modeling exercise [94].

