### Project timeline

The project began in February 2021, focusing first on recruitment and developing the initial fiscal mapping process prototype. When we completed this protocol in October 2021, we had finished recruitment and were conducting initial training with participating agencies; pilot-testing and data collection will take place over the subsequent 12 months. We will iteratively analyze data and incorporate it into the fiscal mapping process throughout pilot-testing, with the goal of finalizing the tool by the end of the project period (January 2023). This timeline coincides with the COVID-19 pandemic, but all project activities were planned to be conducted virtually which helped to minimize disruption.

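### PSAT, PRESS and intentions to sustain are first rated at months 4–5, after training and coaching have begun, so their change shows early-to-late use and not before-to-after

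*Protocol article*

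**What the plan says.** The Research design section sets the purpose: "Aim 2 is to evaluate the preliminary impact of the fiscal mapping process". The Aim 2 analysis section makes case studies the main method and adds a quantitative element: "we will examine if quantitative data follow expected contrasts and patterns over time". Its example is that fiscal mapping may be used more effectively where strategic planning capacity is higher or rising.

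The standardized measures of sustainment capacity and outcome are PSAT, PRESS and intentions to sustain. Table 2 lists them only in the row "Focus groups (months 4–5, months 10–11". The Focus groups section places them after each discussion: "Afterwards, participants will complete a brief web-based survey rating".

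On exposure, the Project timeline gives the position in October 2021 as follows: "we had finished recruitment and were conducting initial training with participating agencies; pilot-testing and data collection will take place over the subsequent 12 months". The Initial training section describes a session that "allows agency representatives to leave training with an in-progress fiscal map". The Monthly coaching section says that "each coach will provide monthly coaching sessions for 1 year with the service agencies for which they led training".

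Web survey #1 (months 1–3) carries Delphi Round 1, feedback on the financing strategies and, for service agency representatives, the Implementation Climate Scale and the Agency Financial Status Scales. It does not carry PSAT, PRESS or intentions.

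**The concern.** All ten agencies receive the tool and there is no comparison group. On the quantitative side, evidence of impact therefore has to come from change within agencies or from contrasts between them. If both waves follow exposure, two things are lost.

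First, any shift between the start of training and months 4–5 falls outside what the scales can show. Early movement is plausible: PSAT measures the domains of the Public Health Sustainability Framework, strategic planning is the central one, and strategic planning is what the training works on.

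Second, the plan's own example becomes hard to read. If capacity is first rated after months of use, a higher value at an agency that uses the tool well may be the reason for good use or its result.

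The Discussion makes a later randomized trial depend on promising evaluation outcomes, and public release of the tool depend on the findings, so the reading of these scales has consequences.

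**Working it through.** The plan gives no figure to reproduce. The check is of the timeline.

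1. **Where month 1 lies.** Table 2 does not define it.
   - Counted from project start (February 2021 = month 1), months 4–5 are May–June 2021 and October 2021 is month 9. The first focus groups would then precede training. That conflicts with the Project timeline, which puts data collection in the 12 months after October 2021, and with the Focus groups section, where participants discuss their experience of using the tool.
   - Counted from the pilot year (for example November 2021 = month 1), months 4–5 are February–March 2022 and months 10–11 are August–September 2022. This fits both sections and is the only coherent reading.

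2. **Internal consistency.** The Focus groups section puts each group about 3 months after a survey.
   - Survey #1: months 1–3 plus 3 = months 4–6, against months 4–5 in Table 2.
   - Survey #2: months 6–9 plus 3 = months 9–12, against months 10–11.
   - The two agree, so the schedule is not a misprint.

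3. **Exposure before the first rating.** The training comes first. Coaching is monthly for a year, about 12 contacts.
   - If coaching starts in month 1: 3 contacts (rating early in month 4) to 5 (rating late in month 5).
   - If coaching starts in month 2 (assumption): 2 to 4.
   - Overall 2 to 5 of 12, that is 2/12 = 17% to 5/12 = 42%.

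4. **Gap between the two waves.** Shortest 10 − 5 = 5 months, longest 11 − 4 = 7 months.

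5. **Scheduled pre-training administrations of PSAT, PRESS or intentions.** None in Table 2 or in the sections on surveys, focus groups, webinar or field notes.

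6. **What does predate training.** The recruitment section says that the nomination and application process gathered quantitative and qualitative data on each agency, to be used in the case studies. It does not name the instruments.

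**The case against.** The strongest reply is that this is an exploratory comparative case study and not a before-after trial. The evaluation rests mainly on qualitative material. Focus group participants are asked directly how the tool has affected capacities and outcomes, and training notes, coaching logs and documents add to that. The article never defines a before-after score change as an outcome, and it calls power limited and most results preliminary. Even a true baseline in ten uncontrolled agencies would not isolate impact; the article leaves that to a later trial. All of this stands, and it lowers the severity. It does not remove the point, because the analysis section commits to reading quantitative patterns over time, and the limits stated in the Discussion stress the two-year timeframe without mentioning that the first scale ratings come after exposure.

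Nor is this a detail left to a fuller document: Table 2 fixes both the measures and the timing.

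Three stronger readings are tempting and not supported:
- **That Aim 2 has no pre-exposure information at all.** Application data predate training. The supportable statement is that no section schedules these three scales before exposure.
- **That a fast-acting tool would look inert.** The scales might miss an early gain, but the interviews and field notes could still report it.
- **That a definite share of the effect is lost.** This would need an effect curve over time. The documents give none, and assuming a linear one only restates the calendar.

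**Conclusion.** The point holds for the three standardized scales, as a moderate design weakness. Both scheduled waves follow training and, for the first, roughly 2 to 5 coaching contacts. Their difference describes change over 5 to 7 months within the pilot. It does not describe change from before to after the tool, and a high first-wave value cannot be separated from an early effect.

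This rests on two assumptions: that the months in Table 2 count from the pilot year, which the other sections all but require, and that coaching runs once a month from month 1 or 2. The conclusion that both waves are post-exposure does not depend on the exact number of contacts. How much change falls before months 4–5 cannot be estimated from the documents.

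**What to change.** - Add PSAT and PRESS, for everyone who will rate them later, and the intentions item, for service agency representatives, to web survey #1. Send it at the start of its window, and before training for any agency not yet trained.
- For agencies already trained, record the time since training. Label the value as an early-exposure rating or, for PSAT and PRESS only, as a retrospective pre-training rating. A recalled intention about the coming year would be hard to interpret.
- Do not pool these values unmarked with true pre-training values, since comparison across agencies is the main analysis.
- Keep the waves at months 4–5 and 10–11. State in the analysis section that the difference between them, taken alone, reflects only change within the pilot.

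The cost is modest: no new contact or staff, at most 48 respondents, of whom 24 also answer the intentions item. Survey #1 already takes 20–30 minutes and would become longer. PRESS has three items; the article does not give the length of PSAT. Funders and intermediaries would need to know by then which agency they are rating. Retrospective ratings bring recall error. Ratings in survey #1 would also not follow a group discussion, as the later ones do, and this difference should be noted when change is described.
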